##### Data Collection

To user-test, a consultant with experience will administer a questionnaire to determine whether the individual can understand selected information key points. A short semi-structured interview will be conducted to explore the participants’ views.

After each round of testing, the findings will be analysed to overcome identified problems. The process will be repeated until all problems have been satisfactorily resolved. Participants will also be interviewed regarding the degree of satisfaction and the strengths and weaknesses of the PDA. All interviews will be audiotaped.

##### Analysis

The audiotapes will be analysed independently by two researchers. We will categorise and organise the data as the initial thematic analysis, which will allow us to identify recurrent patterns and explore the meanings and processes associated with the interview data.

#### 2.1.4. Phase 4: Validation of the PDA

This will be carried out in order to assess the SDM outcomes of the PDA implementation in an experimental study in primary health centres compared with usual care, including an evaluation of the underlying process.

##### Participants

Clusters (primary health centres in the two Valencian Health Departments) will be randomised to use the PDA or usual care by using a computer-generated list based on the number of collaborating general practitioners. Based on a logistic regression, a cluster size of 12 clusters, each enrolling 30 patients (360 observations), will achieve 80% power (95% CI) to detect a mean difference of 0.35 between the groups in decisional conflict scores. Patients will be considered candidates for screening by their clinicians according to the European Society of Urology recommendations [23].

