### 2.2. Data Collection

The study coordinator will enrol health care centres (clusters), and general practitioners will enrol patients. We will provide clinicians with one education session on the rationale for SDM in each centre. The intervention (PDA) will be applied at the cluster level to avoid contamination. Patients will be blind to the group designation. Factors influencing outcomes will be assessed at three levels: the health centre cluster, individual general practitioner and patient. The clinicians in the control group will proceed as in usual care. A research assistant blinded to the group assignment will collect information on patients’ demographic and clinical characteristics and on whether a PSA test was ordered from the medical records. A follow-up telephone survey of the patients will be conducted within 3 weeks of the visit in order to assess: (a) whether screening took place; (b) knowledge regarding prostate cancer (Knowledge of the Prostate Cancer tool [26]); (c) decisional conflict (ten-question Decisional Conflict Scale [27]) and (d) discussions regarding screening between patients and clinicians and the satisfaction with the screening decision (Satisfaction with Decision Scale [28]).

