### 2.5. Ethics and Dissemination

The PROSHADE protocol was approved by the CEIC Sant Joan d’Alacant (20/041) on 8 January 2021. All participants will give oral/written informed consent prior to entry to the study by a member of the study team and will be made aware that participation is strictly voluntary. Participants may withdraw from the study at any time. The research adopts the principles of open science, and the findings will be published ensuring the participants’ confidentiality.

**Trial registration:** Clinical trials: NCT05187949 (https://clinicaltrials.gov/) (accessed on 1 July 2022).

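### The stated 80% power counts every one of the 360 enrolled men as a scored observation, so it assumes a 100% response to the later telephone survey

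*Protocol article*

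**What the plan says.** Three places in the protocol article bear on this.

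- **Section 2.1.4, Participants (Phase 4).** The trial has "a cluster size of 12 clusters", "each enrolling 30 patients (360 observations), will achieve 80% power". The target is "to detect a mean difference of 0.35 between the groups in decisional conflict scores". The sentence gives no SD, ICC, allocation ratio or expected response.
- **Section 2.2, Data Collection.** "A follow-up telephone survey of the patients will be conducted within 3 weeks of the visit". Decisional conflict is item (c) of that survey. The separate extraction from medical records covers patient characteristics and whether a PSA test was ordered, so it cannot supply a missing score.
- **Section 2.5, Ethics and Dissemination.** "Participants may withdraw from the study at any time". This is a general statement for the whole project.

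**The concern.** The sample-size sentence gives both an enrolment number and an observation number and makes them equal. Enrolment happens at the centre, through the general practitioner. The score the trial is sized on arises later, by telephone, and only for men who are reached and answer. The two counts coincide only if nobody is lost.

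What is at stake is how a null or imprecise result would be read. A reader would set it against 80% power for a difference of 0.35, whereas with any non-completion the design delivers less than that on the plan's own inputs.

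**Working it through.** **Inputs from the article:** 12 centres; 30 men enrolled per centre; 360 observations; 80% power; difference 0.35; a 95% level, read as two-sided α = 0.05.

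**Assumptions, because the article does not give them:** 6 centres per arm; ICC from 0 to 0.10; non-completion of 10%, 20% or 30%, spread evenly over centres. These leave m = 27, 24 or 21 scored men per centre.

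**Step 1. Implied loss.** 12 × 30 = 360 enrolled and 360 observations, so the implied loss is 0%.

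**Step 2. Can the 80% be reproduced?** Not uniquely.
- With SD = 1 and no clustering, 180 men per arm give 0.35 × √(180/2) = 3.320. Power is Φ(3.320 − 1.960) = 91.3%.
- With a design effect 1 + (m − 1) × ICC and SD = 1, 80% at m = 30 needs ICC ≈ 0.014.
- With ICC = 0, 80% needs SD ≈ 1.185.

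Several input pairs therefore give 80%, and the article does not say which was used.

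**Step 3. Take 80% as exact at 30 scored men per centre.** The standardised signal at m = 30 is then 1.960 + 0.842 = 2.802. With m scored men per centre it becomes

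2.802 × √{ [(1 + 29 × ICC)/30] ÷ [(1 + (m − 1) × ICC)/m] },

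and power is Φ(that value − 1.960). The SD cancels.

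Two examples at 20% loss (m = 24):
- ICC 0: 2.802 × √(24/30) = 2.506; Φ(0.546) = 70.7%.
- ICC 0.10: 2.802 × √[(3.9/30) ÷ (3.3/24)] = 2.802 × √(0.1300/0.1375) = 2.724; Φ(0.764) = 77.8%.

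| ICC | 10% loss | 20% loss | 30% loss |
|---|---|---|---|
| 0 | 75.7% | 70.7% | 65.0% |
| 0.01 | 76.7% | 72.8% | 68.1% |
| 0.02 | 77.3% | 74.1% | 70.2% |
| 0.05 | 78.3% | 76.3% | 73.7% |
| 0.10 | 79.0% | 77.8% | 76.2% |

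Using a t reference with 10 degrees of freedom, recalibrated to 80% at m = 30, changes these by no more than 0.2 percentage points. The drop is smaller at higher ICC because loss shrinks the centres without reducing their number.

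**Step 4. Detectable difference at 80% power, 20% loss.**
- ICC 0: 0.35 × √(30/24) = 0.39.
- ICC 0.05: 0.35 × √[(2.15/24) ÷ (2.45/30)] = 0.35 × 1.047 = 0.37.

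**The case against.** The strongest reply is that this is a condensed article. A non-response allowance and a replacement rule are details that a full protocol would normally hold, and their absence here would be no finding. The wording might also be shorthand for 30 evaluable men per centre, with enrolment continuing until that is met. The first part is right as far as it goes: a missing allowance alone is no error. But the article is not silent. It prints both numbers and equates them. If the full protocol enrols more to cover loss, the enrolment figure in the article is wrong; if 360 is the enrolment, the observation figure is wrong. The sentence needs correcting on either reading.

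Other parts of the reply stand and limit the point:

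- **The 80% cannot be verified.** A reader might infer that power falls short whatever SD and ICC were used. That follows only if 80% is exact at 360. With SD = 1 and no clustering, 129 men per arm suffice for 80%, so 180 per arm would absorb about 28% loss (1 − 129/180).
- **No appreciable loss is documented.** A reader might take the withdrawal sentence as evidence that many scores will be missing. It is a general ethics statement covering all four phases, and Phase 4 follow-up is a single call soon after the visit to men who consented. It shows that loss is possible, not how large it will be.
- **Replacement by easier-to-reach men.** A reader might fear that practitioners will top up their numbers this way. The article describes no replacement, so this is speculation.
- **The lowest figure is an extreme.** The 65% needs both 30% loss and ICC 0, an unlikely value in a cluster trial.

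**Conclusion.** The point holds as a misstatement of what the 80% refers to. Power is attached to 360 scores, and that number is reached only if all 360 enrolled men complete the survey.

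Its size is modest. Over ICC 0 to 0.10, the drop from 80% is about 1–4 percentage points at 10% loss, 2–9 at 20% and 4–15 at 30%. This rests on 80% being exact at 30 scored men per centre, 6 centres per arm, even loss across centres, and assumed loss rates and ICCs. The direction is certain under the first of these assumptions; the amount is not.

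The documents do not support the stronger conclusion that the trial is underpowered. That would need the SD, the ICC and an expected response rate, and none is given.

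**What to change.** In the Phase 4 sample-size sentence:

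1. Describe 360 as the number of men enrolled, not as the number of observations.
2. Give the expected number of completed telephone surveys, with the assumed non-completion rate. At an assumed 20%, for example, this is 0.80 × 360 = 288, or 24 per centre.
3. Restate on that number either the power for 0.35 or the difference detectable with 80% power, using the SD and ICC from the plan's own calculation.
4. If 360 was intended as completed surveys, leave the observation count and correct the number enrolled per centre instead.

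The cost is a sentence or two and a slightly less favourable stated figure. Restating the power on an enrolment of 360 needs no extra men. Under item 4, the text would only record the larger enrolment already intended. Section 2.4 says that the team is only starting to design the knowledge surveys, so on that status the correction comes before any Phase 4 data.

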### 2.2. Data Collection

The study coordinator will enrol health care centres (clusters), and general practitioners will enrol patients. We will provide clinicians with one education session on the rationale for SDM in each centre. The intervention (PDA) will be applied at the cluster level to avoid contamination. Patients will be blind to the group designation. Factors influencing outcomes will be assessed at three levels: the health centre cluster, individual general practitioner and patient. The clinicians in the control group will proceed as in usual care. A research assistant blinded to the group assignment will collect information on patients’ demographic and clinical characteristics and on whether a PSA test was ordered from the medical records. A follow-up telephone survey of the patients will be conducted within 3 weeks of the visit in order to assess: (a) whether screening took place; (b) knowledge regarding prostate cancer (Knowledge of the Prostate Cancer tool [26]); (c) decisional conflict (ten-question Decisional Conflict Scale [27]) and (d) discussions regarding screening between patients and clinicians and the satisfaction with the screening decision (Satisfaction with Decision Scale [28]).

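### GPs enrol patients in centres allocated to an open decision aid or usual care, so the two arms may recruit different men and the comparison risks recruitment bias

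*Protocol article*

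**What the plan says.** All of this is in the Protocol article.

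- **Unit of randomisation** (section 2.1.4, Participants): "Clusters (primary health centres in the two Valencian Health Departments) will be randomised to use the PDA or usual care". Twelve clusters each enrol 30 patients, 360 in all, to detect a mean difference of 0.35 in decisional conflict scores.
- **Candidacy** (same section): "Patients will be considered candidates for screening by their clinicians", with the cited European urology recommendations as the yardstick.
- **Enrolment** (section 2.2, Data Collection): "The study coordinator will enrol health care centres (clusters), and general practitioners will enrol patients".
- **Delivery** (section 2.2): "The intervention (PDA) will be applied at the cluster level to avoid contamination". For the other arm, "The clinicians in the control group will proceed as in usual care".
- **Blinding** (section 2.2): "Patients will be blind to the group designation", and "A research assistant blinded to the group assignment will collect information on patients’ demographic and clinical characteristics". Blinding of GPs is not described.
- **Analysis** (section 2.3): patient and GP characteristics are compared between clusters by standard tests. No patient covariate is named for the outcome model.

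**The concern.** Randomising centres balances centres, in expectation. It does not balance the men whom those centres go on to recruit. If the recruiter knows the arm and has any latitude over whom to approach, the case mix can drift apart between arms after randomisation.

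It matters here because the Background (section 1) itself names education, age and prior PSA testing as factors that can influence a man's decision, and says that men do not react uniformly to screening information. A GP knows or can guess these traits. They plausibly bear on every Phase 4 outcome: decisional conflict, knowledge, satisfaction and whether screening took place. The GP's task also differs by arm, since one group introduces a new tool and the other carries on as before. A difference in who is enrolled would then be read, in part, as an effect of the PDA.

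**Working it through.** **1. Who acts when, and who is blinded**

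| Step | Who acts | Blinded? |
|---|---|---|
| Centre enrolled | Study coordinator | Not stated |
| Man judged a candidate | His clinician, by the cited guideline | Not stated; not possible once an open PDA is in use |
| Man enrolled | GP | As above |
| Visit, with or without PDA | GP and patient | Patient only |
| Patient characteristics and PSA order collected | Research assistant | Yes |

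Both stated blinding measures act somewhere other than the two selection steps. Two links are inferred: that GPs know the allocation, and that they enrol after it is made.

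**2. The plan's own figure**

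12 × 30 = 360 is correct. The 80% power cannot be confirmed because no SD or intracluster correlation (ICC) is given. Assuming SD = 1, 180 per arm and a two-sided 5% test, power is 91% at ICC = 0. It falls to 80% at an ICC of about 0.014 (design effect 1 + 29 × 0.0139 = 1.403). The recruitment point does not depend on this; it only supplies a working standard error.

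**3. Illustrative size of bias**

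All inputs below are assumptions. Treating 0.35 as SD units is also an assumption, because the article gives it as a difference in scores.

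*Route A, continuous trait:* bias = shift between arms (SD) × correlation with the score.
- Low: 0.25 × 0.2 = 0.05 SD, and 0.05 / 0.35 = 14% of the target.
- Middle: 0.5 × 0.3 = 0.15 SD, and 0.15 / 0.35 = 43%.
- High: 0.5 × 0.5 = 0.25 SD, and 0.25 / 0.35 = 71%.

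*Route B, binary trait:* bias = effect of the trait on the score (SD) × difference in its prevalence between arms.
- Low: 0.3 × 0.10 = 0.03 SD, and 0.03 / 0.35 = 9%.
- High: 0.5 × 0.30 = 0.15 SD, and 0.15 / 0.35 = 43%.

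Together the routes span 0.03 to 0.25 SD.

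**4. Effect on the false-positive rate (Route B, no true effect)**

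SE = √(2 × design effect / 180). Rate = Φ(−1.96 + bias/SE) + Φ(−1.96 − bias/SE).

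| ICC | Design effect | Rate at 0.03 SD | Rate at 0.15 SD |
|---|---|---|---|
| 0 | 1.00 | 5.9% | 29.6% |
| 0.0139 | 1.403 | 5.7% | 22.5% |
| 0.05 | 2.45 | 5.4% | 14.9% |

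For example, at ICC 0.0139 the SE is √(2 × 1.403 / 180) = 0.125. The bias/SE is 0.15 / 0.125 = 1.20, and the rate is about 22%.

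Sample size does not enter the bias formulas, so recruiting more men would not reduce the bias.

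**The case against.** The case on the other side has real force on several points.

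- **The order of events is not stated.** The article never says that patients are enrolled after the centre's allocation is known. That is the natural reading, but it is an inference, and the point is worded as a risk for that reason.
- **A journal article condenses.** Consecutive invitation, screening logs and consent timing usually sit in the full protocol, and their absence here is no finding. What the article does fix is who judges candidacy, who enrols and who is blinded, and that arrangement carries the risk.
- **The guideline limits discretion.** It narrows who can count as a candidate. It does not settle which eligible men are approached for the 30 places in each centre.
- **Consent.** Section 2.5 has a study-team member take consent, but that does not change who identifies and enrols the men.
- **Measured traits can be handled.** Section 2.2 collects demographic and clinical characteristics, and age, education and prior PSA testing could be adjusted for. A reader might infer that selection can never be separated from the PDA effect. That holds only for unmeasured traits such as engagement.

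A reader might also infer a particular pattern, with PDA centres picking engaged men and control centres enrolling men who already want a PSA test. Nothing in the article supports this. The education session on shared decision making, which section 2.2 places in each centre, may prompt control GPs too, so the direction is unknown.

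**Conclusion.** The point holds as a risk of identification or recruitment bias created by the stated recruitment arrangement. It rests on two inferences: GPs know their centre's allocation, which is unavoidable with an openly used aid, and they enrol with that knowledge, which is the natural reading of sections 2.1.4 and 2.2. Neither the planned blinding nor cluster randomisation covers the selection step. Testing characteristics between clusters may reveal an imbalance in measured traits but does not prevent one.

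The documents do not support the stronger claim that the comparison is biased, or biased by a given amount. The range of 0.03 to 0.25 SD is an illustration under assumed inputs and an assumed SD scale. A single figure such as 43% of the target should not be quoted as an estimate. The bias could inflate or hide a PDA effect. The change is worth making before Phase 4 because it is cheap and the study is still designing its knowledge surveys (section 2.4).

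**What to change.** In sections 2.1.4 (Participants) and 2.2:

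1. Require each centre to invite consecutive men who meet the same fixed criteria, based on the recommendations already cited and applied identically in both arms, until 30 are enrolled. Where possible, identify these men before the centre's allocation is disclosed.
2. Keep a log in every centre of men eligible, invited and enrolled, and compare the counts by arm.
3. Adjust the arm comparison for patient factors fixed before the visit (age, education and prior PSA testing), and name these among the data to be collected.

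The research assistant who collects outcomes should stay out of recruitment. Working in the centres at that stage could reveal the allocation. Recruitment before the visit could also prompt men about PSA and so alter usual care.

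The cost is log-keeping and slightly slower recruitment. Selection on unmeasured traits such as engagement would be reduced by consecutive invitation but only partly controlled, and the report should say so.

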### 2.3. Statistical Analysis

Patients’ and general practitioners’ characteristics between clusters will be analysed using the *t* test or Wilcoxon rank sum test for the continuous variables and the χ^2^ test for the categorical variables. Modified Poisson regression with a sandwich estimator for standard errors will be used to estimate the relative risk, accounting for clustering by site using fixed effects.

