Several randomised clinical trials have evaluated PDAs for PC screening, mainly among primary care patients, with contradictory results. According to a recent meta-analysis [11], the available PDAs face both design and implementation challenges, and although they improve men’s knowledge regarding PSA benefits and risks, they fail to promote SDM. Hence, how to design and implement PDAs in PC screening represents a large gap in the existing literature. The meta-analysis identified the lack of consideration of the patients’ perspective as the main concern in the design and implementation of these previous PDAs, resulting in a poor analysis of the best strategy to help patients to evaluate which benefits and harms are most important to them. There are many factors that may determine whether men receive screening, including their personal preferences and factors related to their clinician. Recent research has highlighted that men do not have uniform reactions to PC screening information: some prefer an active approach and want to receive PSA screening after being informed, while others prefer not to receive it [12]. There are also some PC screening determinants which can influence the patient’s decision such as education, age and prior PSA testing, but these factors have not been adequately addressed in previous decision-aids. Some studies have proposed the use of a well-calibrated risk prediction model to define PSA thresholds for identifying or excluding advanced PC as an aid to personalise the management of the diagnostic workup. The proposed PSA thresholds, being associated with the related predictive values, may allow for an individualised approach to the diagnostic workup, assisting patients in making an informed decision [13].

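### Section 2.3 tests patients' and GPs' characteristics with methods that ignore clustering; describe them by arm instead, and handle imbalance by prespecified adjustment in a model that can estimate the arm effect

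*Protocol article*

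**What the plan says.** The Phase 4 Participants section sets the unit of allocation: "Clusters (primary health centres in the two Valencian Health Departments) will be randomised to use the PDA or usual care". On how the allocation is generated, that section says only that it is done "by using a computer-generated list based on the number of collaborating general practitioners". It plans 12 centres with 30 patients each, 360 in all.

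Section 2.3 then gives two sentences of analysis.

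- The first says that patients' and GPs' "characteristics between clusters will be analysed using the" tests that it goes on to list: a t "test or Wilcoxon rank sum test for the continuous variables", followed by a χ² "test for the categorical variables". It names no arms, gives no purpose and makes no allowance for clustering.
- The second concerns the effect: "Modified Poisson regression with a sandwich estimator for standard errors will be used to estimate the relative risk". It deals with the centres by "accounting for clustering by site using fixed effects". It names no covariates and does not say whether the model is adjusted.

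Two other places bear on the remedy. Section 2.2 has GPs enrol the patients, collects patients' demographic and clinical data, and plans to look at influences on outcome at centre, GP and patient level. The Background says that men's screening decisions can be influenced by "education, age and prior PSA testing, but these factors have not been adequately addressed in previous decision-aids".

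**The concern.** Patients in one centre tend to resemble each other, and so may the GPs who work there. A test that treats them as independent overstates the information about differences between randomised groups, so its p-values come out too small. The effect sentence in Section 2.3 recognises clustering; the sentence on characteristics does not.

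With only 12 centres, and with GPs deciding whom to enrol, some real imbalance is plausible. A significance test does not remove it. The tests could flag differences that chance allocation of whole centres produces routinely, while leaving any real difference untouched. Prespecified adjustment can reduce the influence of imbalance in measured factors, but only in a model from which an arm effect can be obtained.

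**Working it through.** The article gives no figure of its own on this point to reproduce. Its 80% power statement is a separate matter and is not used here.

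**Inputs from the article.** 12 centres, m = 30 patients per centre, whole centres allocated to one arm (Phase 4 Participants).

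**Assumptions.** Six centres per arm (the ratio is not stated), a two-sided 5% level for the tests, and ICC values of 0.01 to 0.10 for a patient characteristic (no ICC is stated).

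**Step 1: literal reading, between centres.** The t test and the Wilcoxon rank sum test compare two groups, so neither can compare 12 centres. A χ² test can be laid out for 12 centres, but it would then show whether centres differ, which says nothing about the arms.

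**Step 2: likely reading, between arms.** The variance of an arm mean is inflated by the design effect DE = 1 + (m − 1) × ICC = 1 + 29 × ICC. A test that ignores this has real size 2 × [1 − Φ(1.96 / √DE)].

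| ICC (assumed) | DE | 1.96 / √DE | Real size of nominal 5% test |
|---|---|---|---|
| 0.01 | 1.29 | 1.73 | 8.4% |
| 0.02 | 1.58 | 1.56 | 11.9% |
| 0.05 | 2.45 | 1.25 | 21.1% |
| 0.10 | 3.90 | 0.99 | 32.1% |

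A simulation with 4,000 runs and six against six centres of 30 agrees. At ICC 0.01, 0.05 and 0.10 the t test rejected in 8.3%, 21.2% and 32.7% of runs, and the χ² test in 8.2%, 22.0% and 33.8%. These figures are for patient characteristics. The article does not give the number of GPs per centre, so no size can be put on the tests of GP characteristics.

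**Step 3: can adjustment be added to the stated model?** Arm is constant within a centre, and so is the number of collaborating GPs. Ranks of the design matrix:

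| Terms | Columns | Rank |
|---|---|---|
| 12 site effects + arm | 13 | 12 |
| 12 site effects + arm + number of GPs | 14 | 12 |
| 12 site effects + arm + number of GPs + age | 15 | 13 |
| Intercept + arm + number of GPs + age, no site effects | 4 | 4 |

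With site fixed effects, neither arm nor number of GPs adds anything that can be estimated. Age adds one rank but does not release the arm effect. Without site fixed effects all four terms are estimable, provided that clustering is handled in another way.

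**The case against.** The strongest reply is that this concerns a descriptive table. The 8% to 32% is the error rate of p-values for characteristics. It is not the type I error of the trial, and Section 2.3 does not say that the tests judge comparability, choose covariates or trigger adjustment. That stands: the purpose is inferred, and the reach is limited. It does not make the tests valid as written.

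A reader might go further and infer that the effect model leaves out known determinants. The article does not support this. It never says that the model is unadjusted, and a covariate list is commonly left to a fuller protocol or SAP, which is not shown. The Background passage is about influences on the screening decision and how previous aids dealt with them. It does not say that these factors predict decisional conflict, the outcome that sizes the trial, and Section 2.2 does not name education or prior PSA testing among the recorded data.

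A reader might also infer that the model ignores a randomisation factor. This is not supported either. The site fixed effects already absorb the number of GPs (Step 3), and the wording about the allocation list does not establish that the number was a stratification factor.

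Finally, a gain in precision from adjustment cannot be claimed at any given size. Nothing in the article says how much outcome variance these covariates explain. Covariates that explain only within-centre variance also help the arm contrast less than they help at patient level. At an assumed ICC of 0.05 and 30 patients per centre, the within-centre part is (0.95/30) / (0.05 + 0.95/30) = 39% of the variance of a centre mean.

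**Conclusion.** The point holds for the stated tests. Under the literal reading the t and rank sum tests do not fit 12 centres. Under the likely reading a nominal 5% test of a patient characteristic has a real size of about 8%, 12%, 21% or 32% at ICC 0.01, 0.02, 0.05 or 0.10. Those sizes rest on the assumed ICCs, on 30 patients per centre and on a six-against-six split. The direction holds for any positive ICC.

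The consequence is misleading descriptive p-values, not a biased effect estimate. Adjustment for patient characteristics is a sensible improvement with 12 centres and enrolment by GPs; the article's silence on covariates is not itself an error. Adjustment cannot yield an arm effect while site fixed effects remain in the model.

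**What to change.** 1. Replace the tests in the first sentence of Section 2.3 with descriptive tables by arm, at centre, GP and patient level, without p-values.
2. Replace the site fixed effects by a random centre effect, or by GEE with cluster-robust standard errors, with a small-sample correction for 12 clusters, so that the arm effect can be estimated.
3. In that model, prespecify adjustment for patient age and, where they are recorded, education and prior PSA testing. Add the number of collaborating GPs only if it was used to constrain the randomisation, and sparingly. Keep the unadjusted model as sensitivity analysis.

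The cost is a change of analysis wording and slightly more analysis work. If the number of GPs is included, it takes about one of the 12 − 2 = 10 centre-level degrees of freedom.

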In addition, the process carried out to develop this SDM strategy in PC screening could guide SDM research in other medical practice areas. There is little consensus on which PDA format is most effective, and it is a challenge to develop patient decision aids that can be routinely used in practice. In 2003, the International Patient Decision Aid Standards [24] established a consensus on quality standards between PDA developers. However, questions have been raised about its validity in practice. With this project, we will establish an empirical evaluation of this procedure, which is generically described, to develop a PDA. According to the available recommendations, we will assess patients’ and clinician’s decisional needs and knowledge to obtain a range of perspectives on the information that patients and clinicians need to have in order to have a maximal influence on SDM outcomes. Moreover, and given that gaps have been identified in presenting probabilistic PSA information to patients, we will contextualise relevant information for patients such as the likelihood of having a false-positive result, in order to help them in a decision according to their personal preferences. We will also systematically review the available literature about the barriers and facilitators of PC screening in primary care and develop an initial PDA prototype to be tested in the target population. Finally, we will assess the PDA implementation in clinical practice. To guarantee an adequate implementation in practice, we will measure key outcomes such as decisional conflict or patients’ satisfaction with the screening decision.

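### The trial is sized on a mean difference in decisional conflict scores, but the only stated effect analysis is a relative risk, which cannot estimate that difference

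*Protocol article*

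**What the plan says.** The sample-size paragraph (section 2.1.4, Participants) plans "a cluster size of 12 clusters, each enrolling 30 patients (360 observations" in all, and says that this "will achieve 80% power (95% CI" notation read here as two-sided alpha 0.05) "to detect a mean difference of 0.35 between the groups in decisional conflict scores". The same sentence opens with "Based on a logistic regression".

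Section 2.2 lists the outcome as "decisional conflict (ten-question Decisional Conflict Scale [27", with no threshold for a binary version. It also lists a knowledge tool, a satisfaction scale, whether a PSA test was ordered, whether screening took place, and discussions about screening.

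Section 2.3 has two sentences. The first applies t, Wilcoxon and chi-square tests to patient and practitioner characteristics. The second is the only effect analysis: "Modified Poisson regression with a sandwich estimator for standard errors will be used to estimate the relative risk". That model is further described as "accounting for clustering by site using fixed effects".

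The Discussion confirms that the scale scores matter: "we will measure key outcomes such as decisional conflict or patients’ satisfaction with the screening decision".

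**The concern.** The sizing fixes one quantity, a difference between arms in a mean score. The analysis section fixes another, a ratio of probabilities. Modified Poisson regression can give a relative risk for decisional conflict only if the score is first cut into two categories, and no cut-off is laid down.

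The hypothesis that justified 360 men therefore has no stated test. If the score were forced into the stated model, information would be lost, and the result would depend on a cut-off that could be chosen after the data are seen.

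**Working it through.** **1. The plan's own figure.** Inputs from the article: 12 clusters of 30, so 360 men; difference 0.35; power 80%. Assumed, because not given: 1:1 allocation (180 per arm), two-sided alpha 0.05, SD and ICC.

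Power for two means, normal approximation: Φ(δ / (SD × √(2/n)) − 1.96).

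- SD 1, no clustering: 0.35 / √(2/180) = 3.32, and Φ(3.32 − 1.96) = 91.3%. For 80% power, n per arm = 2 × (1.96 + 0.84)² / 0.35², which is 129 after rounding up, or 258 men in total.
- The stated 80% appears only with inputs the article does not give. Examples are SD 1.185 without clustering, or SD 1 with an ICC of about 0.014 (about 0.005 if a t distribution on 12 − 2 = 10 df is used).

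The 80% can be bracketed but not reproduced.

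**2. Could 0.35 be a difference in proportions, as the mention of logistic regression might suggest?** From a control proportion of 0.30 or 0.50, 31 or 27 per arm would give 80% power without clustering, and 180 per arm would give more than 99.9%. To bring that down to 80%, the design effect would have to be about 180/31 = 5.8 to 180/27 = 6.7. With clusters of 30 (design effect = 1 + 29 × ICC), that is an ICC of about 0.17 to 0.20. Nothing of the kind is stated, so this reading does not explain the figure.

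**3. Does a relative risk recover the sized quantity?** Take a normal score, SD 1, lowered by 0.35 in the decision-aid arm, and call values above a cut-off high conflict. Then p₀ = 1 − Φ(c), p₁ = 1 − Φ(c + 0.35) and RR = p₁/p₀. Power is for 180 per arm, unclustered.

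| Cut-off (SD) | p₀ | p₁ | RR | Power |
|---|---|---|---|---|
| −1 | 0.841 | 0.742 | 0.88 | 64% |
| −0.5 | 0.691 | 0.560 | 0.81 | 74% |
| 0 (median) | 0.500 | 0.363 | 0.73 | 75% |
| 0.5 | 0.309 | 0.198 | 0.64 | 68% |
| 1 | 0.159 | 0.089 | 0.56 | 53% |

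One and the same mean difference gives relative risks from 0.88 to 0.56 depending on the cut-off. Every power figure lies below the 91.3% for comparing means. A log-link Poisson model on the raw score would give a ratio of means, which is neither a relative risk nor a mean difference.

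**4. Clustering terms.** Whole centres are randomised. An intercept, an arm indicator and 11 centre indicators make 13 columns, but with 12 centres (taken as 6 per arm) the matrix has rank 12. Arm is a sum of centre indicators, so its effect cannot be separated from the site fixed effects.

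**5. Why a small-sample correction matters.** For the mean comparison with SD 1:

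| ICC | Design effect | Power, normal | Power, t on 10 df |
|---|---|---|---|
| 0 | 1.00 | 91.3% | 84.8% |
| 0.01 | 1.29 | 83.2% | 75.0% |
| 0.02 | 1.58 | 75.2% | 66.4% |
| 0.05 | 2.45 | 56.4% | 48.3% |

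**The case against.** The best defence is that section 2.3 is a two-sentence condensation. It does not call modified Poisson the primary analysis or tie it to decisional conflict, and the method for the scores may stand in a fuller document. That is fair as far as it goes: a reader might infer that the plan intends to test decisional conflict by dichotomising it, and the article does not say so. What stands is that the article itself fixes a mean difference in one place and a relative risk in another as its only effect measure. A fuller document can agree with both only by adding an analysis that the article does not state.

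It can also be said that the mean-difference wording is the slip, since logistic sizing and a relative risk both point to a binary endpoint. The documents do not settle this, but that route would need a defined cut-off and a new sample-size calculation, and step 2 shows that the present numbers do not fit it.

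A reader might further infer that PSA testing is the only outcome the stated model suits, and that it has no desirable direction. That goes too far. Section 2.2 also collects whether patients and clinicians discussed screening, which may be recorded as yes/no. The Background reports that fewer than 30% of men have such a discussion and names screening discussion among the effects that existing aids fail to show. A relative risk for that outcome is a sensible secondary analysis.

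**Conclusion.** The point holds. As written, the effect analysis cannot test the hypothesis on which the trial was sized, and this follows from the article's own statements, whatever the SD or ICC.

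The size of the loss is illustrative only. With an assumed SD of 1, 1:1 allocation and no clustering, power goes from about 91% to about 75% at a median split. A reader might instead apply the 2/π efficiency of a median split to the stated 80% (2.80 × √0.637 = 2.24, power about 61%) and add that clustering would lower it further. The documents do not support that as a finding: no median split is planned, and the article does not say whether its 80% already allows for clustering.

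**What to change.** In section 2.3, make the decisional conflict score the main analysis: a linear mixed model with a random intercept for health centre and a small-sample degrees-of-freedom correction for 12 clusters, reporting the mean difference with its 95% CI. Use the same model for the knowledge and satisfaction scores.

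Keep modified Poisson regression for the binary outcomes (discussion took place, PSA ordered, screening done) as secondary analyses. Use cluster-robust standard errors with a small-sample correction, and drop the site fixed effects.

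In the sample-size paragraph, replace logistic regression with the method for comparing means in a clustered design, and state the SD and ICC used.

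The cost is wording; no further data are needed for the analysis change. Section 2.4 reports that only the knowledge surveys are being designed, so the change can be made well before Phase 4. If no ICC entered the calculation, stating one may show that 360 men give less than 80% power, and it is better to learn that now.
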